# Improving implementation of evidence-based practice in mental health service delivery: protocol for a cluster randomised quasi-experimental investigation of staff-focused values interventions

**DOI:** 10.1186/1748-5908-8-75

**Published:** 2013-07-02

**Keywords:** Values clarification, Autonomous motivation, Transfer of training

## Abstract

**Background:**

There is growing acceptance that optimal service provision for individuals with severe and recurrent mental illness requires a complementary focus on medical recovery (*i*.*e*., symptom management and general functioning) and personal recovery (*i*.*e*., having a ‘life worth living’). Despite significant research attention and policy-level support, the translation of this vision of healthcare into changed workplace practice continues to elude. Over the past decade, evidence-based training interventions that seek to enhance the knowledge, attitudes, and skills of staff working in the mental health field have been implemented as a primary redress strategy. However, a large body of multi-disciplinary research indicates disappointing rates of training transfer. There is an absence of empirical research that investigates the importance of worker-motivation in the uptake of desired workplace change initiatives. ‘Autonomy’ is acknowledged as important to human effectiveness and as a correlate of workplace variables like productivity, and wellbeing. To our knowledge, there have been no studies that investigate purposeful and structured use of values-based interventions to facilitate increased autonomy as a means of promoting enhanced implementation of workplace change.

**Methods:**

This study involves 200 mental health workers across 22 worksites within five community-managed organisations in three Australian states. It involves cluster-randomisation of participants within organisation, by work site, to the experimental (values) condition, or the control (implementation). Both conditions receive two days of training focusing on an evidence-based framework of mental health service delivery. The experimental group receives a third day of values-focused intervention and 12 months of values-focused coaching. Well-validated self-report measures are used to explore variables related to values concordance, autonomy, and self-reported implementation success. Audits of work files and staff work samples are reviewed for each condition to determine the impact of implementation. Self-determination theory and theories of organisational change are used to interpret the data.

**Discussion:**

The research adds to the current knowledge base related to worker motivation and uptake of workplace practice. It describes a structured protocol that aims to enhance worker autonomy for imposed workplace practices. The research will inform how best to measure and conceptualise transfer. These findings will apply particularly to contexts where individuals are not ‘volunteers’ in requisite change processes.

**Trial registration:**

ACTRN: ACTRN12613000353796.

## Background

Provision of evidence-based services has been a priority in mental health systems in English speaking mental health services for over a decade. This has been driven by a growing awareness and concern that service delivery does not always reflect what is known to be best practice [1]. In response, policy makers have sought ways to narrow this gap and support the translation of research into practice. Within the mental health field, this has included explication of ‘recovery’ as a specific priority both at the policy level and within charters that encompass mental health organisations [2-4]. Recovery can be defined as ‘a way of living a satisfying, hopeful and contributing life’ beyond the limiting effects of mental illness [5].

Worldwide, health systems and the service providers have made significant efforts to re-define programmes and develop staff in alignment with the recovery philosophy and evidence base in order to enhance capacity and further decrease the research-practice gap [6]. The Collaborative Recovery Model (CRM) [7] is one approach that includes evidence-based intervention components, including those that focus on strengths, values, and goal striving [5,8,9]. Despite this, the literature contains numerous examples of disappointing attempts to implement evidence into mental healthcare *e*.*g*., [3,10] and healthcare more broadly [11,12].

Scientific evidence that something is ‘best practice’ is not adequately persuasive in changing the behaviour of staff [13,14]. Translating and using research in practice is a complex process impacting at various organisational levels, including individual staff. Recent enhancements to models of health system change acknowledge the key role of the staff or ‘local actors’ among the numerous contextual and innovation-specific factors [15,16]. Practitioners and managers are not passively persuaded by new practices even when the evidence to support them is sound. Instead, decisions made by managers and practitioners are based on a number of individual factors such as personal experience, clinical judgment, inference, intuition, and advice [6]. People do not implement because of a rational consideration of the evidence alone. Motivation emerges as a key factor [17].

More specifically, the literature on health behaviour change provides a foundation for understanding how to change work behaviours. It is well established within the health behaviour change literature that knowing there is ‘good evidence’ for the benefits of a specific change is a poor predictor of changed behaviour [18]. People are most highly motivated to change when the desired behaviour is something that aligns with their beliefs and values [19]. While this is true for individuals generally, it is likely to be even more salient in professions where individuals are drawn to the work for values-based reasons [20,21]. In a profession where values are central, connecting staff to the ethos in which the change is embedded is likely to be highly important to the promotion of uptake. We argue that values are persuasive in motivating staff to change their practice. In this context, we now discuss values as a key aspect of motivation.

Motivation for change is not an ‘all or nothing’ attribute. Instead, motivation can be understood in terms of the degree to which it is experienced as autonomous (arising from within the individual) or controlled (imposed on the individual by an external regulator) [22]. Within Self-Determination Theory (SDT) [22,23], striving to be self-regulated or ‘autonomous’ is described as a basic human need and something pursued by individuals. Autonomy is defined as the extent to which a behaviour is experienced as internally generated, or self-determined [24]. SDT is a well-supported theory that has underpinned a body of research related to the purposeful goal striving of individuals in a range of contexts *e*.*g*., [25,26]. Goals and behaviours that are experienced as aligned to the values and beliefs of an individual are referred to as ‘self-concordant’ [25]. The self-concordance of goals has also been shown to predict goal success, commitment to the striving process and various aspects of wellbeing [27,28].

### Autonomy in controlled contexts

The human need for autonomy, and feeling that one is choosing to change behaviour, presents a specific challenge for implementation of evidence-based practices in the mental health field. Indeed, this issue emerges in any social context where there is a need to change the behaviour of individuals to comply with an overarching standard or set of social expectations [26,29,30]. There is evidence to suggest that socially controlling contexts are counter-productive to bringing about change, and can forestall implementation [26]. A central question is: How do we create autonomy for specific new practices (a sense that the change has come from within) when the change is imposed as part of the social context? We propose a structured, ongoing values-focused intervention for staff as one approach to enhancing autonomous motivation and therefore implementation of desired workplace change.

Values are defined here as verbal representations of desirable life consequences or ways of behaving that are enduring and pervasive across situations and contexts, [31] which can be enacted in moment-to-moment experience [32]. Values are widely viewed as important predictors and drivers of behaviour [33,34]. While the work-related goals or desired practices necessitated by a change initiative may be made explicit to staff, clarification of the values-base in which such goals are embedded is often overlooked in implementation efforts. By allowing mental health staff to connect with the values and intent of the change to practice, they are also able to identify how these overlay and potentially overlap with their own values as an individual and professional.

In such instances, though the change was not self-generated, it is possible that it will become more fully ‘owned’ as something that fits with the values and beliefs of individual staff members. This process is referred to as ‘integration’ [24], which has been described extensively within psychological and motivational literature [24,26]. Integration represents a shift from a controlled or imposed motivation for behaviour, to a more highly autonomous motivator for change [35]. When integrated, the motivation to act toward a specific goal or end-state is experienced as ‘arising from within’ due to its alignment with personally held values and beliefs. By attending explicitly to the values of staff, we propose an increased autonomous motivation for the desired workplace change and enhanced concordance between the ‘imposed’ practices and the values of individual staff, which will flow through to increased implementation.

Figure 1 demonstrates this proposed shift from low autonomy to a highly autonomous motivation for a key recovery practice, and the anticipated change in implementation:

**Figure 1 F1:**
[figure not shown]
**Proposed increase in autonomy and implementation following values intervention.** This figure aims to illustrate the proposed mechanisms of change and outcomes hypothesised in this research.

### Aims and current research gaps

Autonomy is widely understood as an important factor in the purposeful striving of humans. Autonomy supportive practices are explored within education and developmental contexts [26,30], however there is an absence of research regarding the specific interventions to enhance autonomy in work contexts generally, and none that we are aware of in relation to mental health service delivery. Additionally, the autonomy supportive practices described in previous studies are not structured or standardised, and are therefore difficult to replicate or roll-out on a widespread basis. We propose a specific and structured set of interventions that actively promote clarification of and commitment to personally meaningful values of the mental health worker within the context of imposed organisational change.

## Methods

### Study design and procedure

This research is informed by two previous projects undertaken by this research team, and parallels data collection time frames to enable comparisons of implementation following the addition of the new intervention component. This project is supported by an Australian Research Council grant (LP09900708), with financial and in-kind contributions by the industry partners. Partner organisations are five well-established community-managed organisations involved in the direct provision of services to individuals living with severe and recurrent mental illnesses in the community. The partner organisations will nominate a number of suitable worksites drawn from across their service base to participate in the intervention and research components. We anticipate access to teams across a number of Australian states and government areas, allowing us to compare and control for the effects of geographical variables. In total, approximately 200 mental health workers from across 22 sites will be randomised and referred for intervention.

### Participants

Participants will be randomised by work-site to either the experimental (values) or control (implementation). Cluster-randomisation will be adopted to increase the feasibility of roll out in the organisational setting (*e*.*g*., consistency across what ‘change’ for individuals within a single worksite will look like) and minimise contamination across conditions (*i*.*e*., individual randomisation would likely lead to decreased fidelity to condition due to inevitable interactions between individual staff within teams). A computerised random integer program will be used to refer worksites to condition. Once randomised, staff from within sites will be referred for training and invited to consent to participate in the research process. Blinding will not be used at the participant or worksite level for pragmatic reasons (*i*.*e*., ongoing coaching will require condition-specific protocol) and to maximise fidelity (*i*.*e*., workers will consult with colleagues from worksites in the alternate condition during the course of duties and need to understand the importance of staying within assigned protocol). Information about previous exposure to the training (*i*.*e*., staff who have participated in some CRM training before time one) will be sought to allow screening prior to inclusion in the final data set. Staff who do not consent to participation in research but are within randomised sites will still participate in all intervention components to maximise the benefit of this project for the partners, to promote intervention fidelity within the workplace, and to allow all mental health workers access to contemporary evidence-based practices and techniques.

The intervention will be facilitated by our team and comprises both training (three days) and a 12-month coaching intervention. All teams will receive the same two days of training in the CRM [10]. On the third day of training, they will receive different training activities, according to the condition (values or implementation). In-service coaches (to be trained by our team) will conduct coaching. The in-service coaches will be supported with monthly, group-based coaching-support sessions facilitated by an appropriately skilled project member. Features of each intervention condition are as follows.

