**Figure 2 F2:**
[figure not shown]
**Diagram of the hypothesised relationships between experimental variables.** This figure illustrates direct **(A)** and meditational **(B** and **C)** relationships between experimental (e.g. autonomous motivation) and dependant variables (e.g. implementation).

We will deal with missing data using full-information-maximum-likelihood estimation (FIML). Traditional approaches to missing data (*e*.*g*., list-wise or pair-wise deletion) can lead to considerable bias in parameter estimates. In contrast FIML provides a superior approach to dealing with missing data that uses all the available information for parameter estimation [54].

Standard multiple regression analysis will test for predictors of transfer. In terms of knowledge transfer related to the new workplace practices, we will compare current findings with the pre-post effect sizes extracted from the previous work conducted by the research team [51]. In that study, effect sizes were moderate based on Cohen’s criteria (STARS = 0.25, RKI = 0.52) with a sample size of 75. Given the additional components of this intervention we are expecting slightly higher effect sizes. Data collected in the CRM-VQ will enable comparison of these predictors with participant self-reported implementation of the new work practices.

Work-sampling audits will also be used as an objective measure of transfer. We are anticipating a sample size of 200 at time point one, but have allowed for a more modest sample size of 100 in calculating power analyses. In our previous study, we found 37% of people transferred training. With this information we are able to estimate the percentage of people who need to demonstrate transferred practices in work samples in order to show a significant increase in the proportions between the former and present studies. Using Z test for proportions we have calculated that we need at least 48 out of the 100 participants to obtain a significant difference at p<0.01 to detect a 10% increase in transfer. We believe this difference is very achievable with the addition of the values-focused interventions.

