A further challenge in this research is to maximise fidelity to condition in this project. As stated above, cluster randomisation by worksite was adopted as a primary means of reducing contamination and enhancing utility and effectiveness of the rollout within the workplace. It is not possible to blind staff to condition, and it is likely there will be a degree of contamination as staff discuss the changes to work practice with colleagues from other sites (*e*.*g*., at training days or meetings). Participants in each condition will be aware that their colleagues may be receiving different components of training in the other condition. To address commitment to condition, both groups receive a strong rationale for the training and coaching approach they receive. Consistency to condition will be monitored specifically via the coaching record form completed alongside monthly coaching sessions. A ‘lessons learned’ and ‘risk register’ will be kept to manage these challenges, and are important to the ongoing development of the implementation literature.

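### Staff are asked for research consent after their worksite has been openly randomised, so who supplies data in each arm can depend on the arm

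*Protocol article*

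**What the plan says.** All the entry steps are in the Participants section of the protocol article.

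- Allocation is by worksite: "A computerised random integer program will be used to refer worksites to condition".
- Consent follows allocation: "Once randomised, staff from within sites will be referred for training and invited to consent to participate in the research process".
- Allocation is open: "Blinding will not be used at the participant or worksite level for pragmatic reasons". The reasons given are that coaching must follow the condition's own protocol and that staff need to know which protocol to keep to.
- Declining does not change treatment: "Staff who do not consent to participation in research but are within randomised sites will still participate in all intervention components".
- Prior CRM training is asked about, and this information "will be sought to allow screening prior to inclusion in the final data set". The criterion is "staff who have participated in some CRM training before time one".

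The Anticipated challenges section adds: "Participants in each condition will be aware that their colleagues may be receiving different components of training in the other condition". The Data analysis section handles missing data by full-information maximum likelihood (FIML). It names autonomy as the mediator between condition and transfer.

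**The concern.** Randomising worksites makes the two sets of sites comparable. It makes the two sets of analysed workers comparable only if workers enter the research independently of arm. Here the entry decision comes after open allocation, which is the usual route to recruitment bias in a cluster trial.

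Consent matters particularly in this trial. Everyone at a site gets the intervention, so consent decides only who contributes data. The Background argues that autonomous motivation drives uptake of new practice, and the same trait could plausibly influence who volunteers for research. If the offer of values work and the offer of barrier-solving work attract different people into the data set, transfer and autonomy will differ between arms without any intervention effect. The objective measures do not escape, because work samples and audited files also come from participating staff.

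**Working it through.** **1. Order of events.** Set side by side, the statements give this sequence: site allocated, staff referred for training, staff invited to consent, with no blinding of participant or site. The stated reasons for not blinding concern delivery of coaching and fidelity. Neither requires the condition to be known when a worker consents. The Participants section says all teams receive the same first two training days and diverge only on day three.

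**2. What the analysis can recover.** FIML uses all available values from enrolled staff. A worker who never consents contributes no questionnaire data, so selection at entry lies outside what it corrects.

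**3. Possible size.** The document gives no consent rates and no between-arm target, so there is no figure to reproduce. The one documented input is the 37% transfer rate in the team's previous study (Data analysis). Everything else below is assumed.

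Assume no true effect. Half the staff are motivated, with transfer rate *a*; half are not, with rate *b*; and (a + b)/2 = 37%. In one arm consent is unrelated to motivation, so observed transfer is 37%. In the other, consent is *c* in motivated staff and *d* in the rest:

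observed transfer = (0.5·c·a + 0.5·d·b) / (0.5·c + 0.5·d)

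| a / b | c / d | Observed | Spurious difference |
|---|---|---|---|
| 47% / 27% | 90% / 70% | 38.2% | 1.2 points |
| 47% / 27% | 90% / 50% | 39.9% | 2.9 points |
| 47% / 27% | 90% / 30% | 42.0% | 5.0 points |
| 57% / 17% | 90% / 70% | 39.5% | 2.5 points |
| 57% / 17% | 90% / 50% | 42.7% | 5.7 points |
| 57% / 17% | 90% / 30% | 47.0% | 10.0 points |

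For example, the last row is (0.5×0.9×0.57 + 0.5×0.3×0.17) / 0.6 = 0.282 / 0.6 = 0.470.

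**4. Direction.** Reversing the pattern reverses the sign. With a = 57%, b = 17%, c = 50% and d = 90%, observed transfer is (0.1425 + 0.0765) / 0.7 = 31.3%, a difference of −5.7 points.

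**5. Whether consent rates would reveal it.** Take a = 50% and b = 24%. If one arm consents 60% of both halves and the other 80% and 40%, the second arm shows (0.20 + 0.048) / 0.6 = 41.3%, a spurious 4.3 points. Overall consent is 60% in both arms, so equal consent rates would not rule out selection.

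**The case against.** The strongest reply is that the bias is possible but not shown to be likely. Staff receive their site's full intervention whether or not they consent, so nobody has to consent to obtain a condition or decline to avoid one. Both arms are active, share two training days and the coaching format, and are each given a rationale for their approach. The text does not say that staff are told their arm at the moment of consent. The article is condensed, and concealment at consent may be described in the full protocol. This stands as a limit on likelihood. It does not remove the problem, because the article itself fixes the order, rules out blinding and gives reasons that do not apply to the consent step.

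A second reply is that planned data allow a partial check. The battery measures autonomy, and files from the six months before the intervention are audited. If time one precedes day three, as a pre-post comparison implies, a between-arm imbalance among consenters could be seen. This also stands, in part. With about 200 staff in 22 sites, chance imbalance is to be expected, and unmeasured differences remain.

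Two stronger readings are tempting, and the document supports neither.

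- A reader might set the spurious difference against the 10% increase in the Data analysis section. That increase compares the present study with the previous one, not the two arms. In step 5 of the working, pooling the equal-sized arms gives (37.0 + 41.3)/2 = 39.2%, a shift of only about 2.2 points on that comparison.
- A reader might count the prior-exposure screen as an equal second gate. Prior CRM training is a fact from before time one that allocation cannot change, and the timing of the screen relative to allocation is only inferred. It is a weaker, secondary concern: the answer comes from unblinded staff, and no blinded application is stated.

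**Conclusion.** The point holds for consent. The article places the consent invitation after open site allocation and states no concealment at that step, so entry to each arm's data set can depend on the arm. FIML does not address this, and the resulting bias could go either way.

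The document does not allow the size to be estimated. The range of about 1 to 10 points between arms rests on four assumptions: no true effect, an even split of motivated and other staff, the assumed transfer contrasts around 37%, and arm-specific consent patterns. It shows what is possible, not what is expected. The document does not support a claim that selection has occurred or will occur.

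**What to change.** For each site, before its condition is disclosed to staff:

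1. list the eligible staff;
2. take research consent;
3. record prior CRM exposure;
4. complete the time-one battery.

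Allocation can still be generated earlier for scheduling, and blinding of delivery is not needed. Apply the prior-exposure screen using only that pre-disclosure record. Keeping prior-exposed staff in the analysis with a covariate is optional and not part of this fix.

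For sites already disclosed, and for staff who join later, report eligible, consenting and excluded counts by site and arm. Also compare time-one autonomy and the pre-intervention file audits between arms, because consent rates alone may not show selection.

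The cost is mainly re-ordering of existing steps and later notice of condition to sites, which also affects planning because coaches are matched within condition. Staff who join after disclosure cannot be covered. With turnover in the field cited as up to 26% a year, that group may not be small. If the full protocol already conceals the condition until consent, stating so in the article would settle the point.
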